### 3.2.3 Criteria for withdrawal

A premature withdrawal or discontinuance shall be construed as withdrawal procedures of the study after the first exposure to study treatment. Withdrawals before that time should be considered "failures of selection."

Patients may be withdrawn from the study at any time at its own request or on the basis of clinical trial investigator. However, patients who request the withdrawal will be strongly encouraged to conduct appropriate tests to make a valid assessment and possible inclusion in the analysis.

The reasons for withdrawal are classified as follows:

**Lack of effectiveness:** The patient showed inadequate response to treatment or deterioration.

**Lack of tolerance:** the dose-limiting intolerance reported by patients or observed by the doctor and found to be "probably" related to study treatment (and therefore does not refer to an aggravation of a preexisting condition).

An adverse event is considered dose limiting toxicity if he understands grade 3 or 4 of the common terminology criteria for adverse events (CTCAE) and is confirmed by a re-assessment within a week.

In the case of treatment of grade 3 transaminase elevation CTCAE, the investigator may decide to continue treatment until no manifestation of liver injury is observed (eg. Jaundice), additional control tests are designed to ensure patient safety.

The CTCAE grade 4 elevation of enzyme (s) impairment (s) or clinical signs of liver damage require immediate discontinuation of study treatment.

**Intercurrent disease:** A disease or condition that occurred or worsened during the study and prevented the completion of treatment and procedures of the study, however, no evidence of a causal relationship to study treatment, the adverse event record corresponding to classify causality as "unlikely" or "not assessable".

**Withdrawal of consent / non-adherence:** The patient, parent or legal guardian withdrew consent or the patient did not adhere to study procedures (must be verified if an adverse event caused withdrawal).

**Other (s) reason (s):** Reason for discontinuation not approached by any of the criteria above, p. ex., moving the patient, other reasons must be specified.

Patients who are withdrawn from the study will not be replaced.

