|                     |                                                                                                                                                                                                     |                       |                                        |
|---------------------|-----------------------------------------------------------------------------------------------------------------------------------------------------------------------------------------------------|-----------------------|----------------------------------------|
| Study Type   | Interventional                                                                                                                                                                                      | Clinical phase | II                                     |
| Study Design | Allocation: Randomized
Control: Active Control
Endpoint Classification: Safety/Efficacy Study
Intervention Model: Parallel Assignment
Masking: Open Label
Primary Purpose: Treatment | Project        | Miltefosine in Cutaneous Leishmaniasis |

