#### 3.3.2 Appointment to the processing and recording

Patients who have been included in evaluations of selection for this research will be documented in an identification list + Patient Record Selection / enrollment.

Each eligible patient will be designated by consecutive numbers, starting at 1 for each age group. The number of patients will be documented in the List of ID + Patient Record Selection / enrollment.

Registration and randomization: the treatment will be allocated according to a randomization list generated by the biostatistics program.

Home Treatment: Treatment should be started up within 2 weeks after completion of evaluations of selection. Otherwise meeting the criteria for eligibility will be restored.

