| - CBC                                                    |       | x               |       | x     | x      | x      | x                       |                                  | x                                |                                   |                                   |                                   |
| - Biochemistry                                           |       | x               |       | x     | x      | x      | x                       |                                  | x                                |                                   |                                   |                                   |
| - Urine type 1                                           |       | x               |       |       |        |        | x                       |                                  | x                                |                                   |                                   |                                   |
| - ECG (control patients)                                 |       | x               |       |       |        |        | x                       |                                  |                                  |                                   |                                   |                                   |
| Vital signs                                              |       | x               | x     | x     | x      | x      | x                       |                                  | x                                | x                                 | x                                 | x                                 |

a Within the 14 days before the 1st dose (except for parasitological examination of lesions, which will be valid within the last 4 weeks)

b It should be evaluated fully when treatment is discontinued. The reason (s) for discontinuation is (are) documented (s). This applies also to patients who withdrew from the study due to any reason.

c Evaluation of selection performed in the first half of the menstrual cycle (<10 days of the cycle) in the case of a negative pregnancy test before randomization, the treatment can be initiated without waiting period.

Evaluation of selection performed in the second half of the menstrual cycle (> 10 days) pregnancy test followed by a waiting period of two weeks, during which they should be used adequate contraception. After the waiting period should be performed a confirmatory test of pregnancy, before randomization.  

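### Section 3.2.3 classes randomised but undosed patients as selection failures and links analysis of patients who request withdrawal to further tests, which can remove patients unequally by arm

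*Protocol*

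**What the plan says.** Section 3.2.3 defines the event that counts as leaving the trial: "A premature withdrawal or discontinuance shall be construed as withdrawal procedures of the study after the first exposure to study treatment". For anyone who leaves sooner it adds: "Withdrawals before that time should be considered 'failures of selection". Randomised patients are not excepted.

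On patients who ask to stop, the same section says that "patients who request the withdrawal will be strongly encouraged to conduct appropriate tests to make a valid assessment and possible inclusion in the analysis". It closes with "Patients who are withdrawn from the study will not be replaced".

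Four other places bear on the point:

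- Section 3.3.2 says that "the treatment will be allocated according to a randomization list generated by the biostatistics program" and, on timing, "Treatment should be started up within 2 weeks after completion of evaluations of selection".
- Footnote c of the flowchart (section 4.6), on women of childbearing age, gives the order of events: "in the case of a negative pregnancy test before randomization, the treatment can be initiated without waiting period". Randomisation therefore precedes the first dose.
- Footnote b of the same flowchart asks for a full evaluation when treatment is discontinued, and extends this to patients who withdraw for any reason.
- The design table gives "Masking: Open Label". Section 3.3.3 describes capsules in one arm and intramuscular or intravenous injection in the other.

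**The concern.** In a randomised comparison, a patient belongs to the trial from randomisation. Section 3.2.3 moves that point to the first dose. Between the two, an open-label patient can know the arm and act on it. If such a patient leaves, the rule files the exit with patients who never qualified, and the randomised group loses a member for a reason that may depend on the arm.

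The sentence on patients who request withdrawal has a similar weakness. It links entry into the analysis to something that happens after randomisation, namely whether the patient agrees to tests. The section's own reasons for withdrawal include lack of effectiveness and lack of tolerance, and both bear on outcome.

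The primary endpoint is the cure rate 6 months after treatment, and the objective is to find miltefosine similar or superior to standard care. A shift in either arm's denominator could therefore matter to the conclusion in either direction. With 30 controls planned, a few exclusions move the control rate visibly.

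**Working it through.** **Reading the rules together**

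1. Section 3.2.3: exit before first exposure means selection failure.
2. Section 4.6, footnote c: randomisation comes before treatment starts.
3. Design table: open label, so the arm can be known once allocated.
4. From 1 to 3, a patient who leaves between randomisation and first dose is a selection failure under the protocol's own wording.
5. Footnote b does not clearly rescue this patient. It covers discontinued treatment and withdrawal, and section 3.2.3 reserves withdrawal for patients already exposed. The no-replacement sentence is likewise limited to withdrawn patients, and the text is silent on replacing selection failures.

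**Plan's own figures**

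Section 3.2 plans 60 miltefosine + 30 control = 90 patients, in a 2:1 ratio. These counts agree with each other. The protocol gives no cure-rate assumption or expected loss, so the size of the effect can only be illustrated.

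**Illustration**

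Assumptions: 70% of all randomised patients are cured in each arm (42/60 and 21/30), and patients who leave before dosing are not cured. With C cured among n randomised and k leavers dropped, the rate changes by

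C/(n − k) − C/n = (C/n) × k/(n − k).

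| Dropped from one arm (k) | Control rate | Shift (points) | Miltefosine rate | Shift (points) |
|---|---|---|---|---|
| 1 | 21/29 = 72.4% | 2.4 | 42/59 = 71.2% | 1.2 |
| 2 | 21/28 = 75.0% | 5.0 | 42/58 = 72.4% | 2.4 |
| 3 | 21/27 = 77.8% | 7.8 | 42/57 = 73.7% | 3.7 |
| 5 | 21/25 = 84.0% | 14.0 | 42/55 = 76.4% | 6.4 |

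If 3 controls and no miltefosine patients are dropped, the comparison reads 77.8% v 70.0%. That is a difference of 7.8 points where the all-randomised difference is 0.

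**Range.** For an assumed cure rate of 50% to 80% and 1 to 5 patients dropped:

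- control shift: from 15/29 − 15/30 = 1.7 points to 24/25 − 24/30 = 16.0 points;
- miltefosine shift: from 30/59 − 30/60 = 0.8 points to 48/55 − 48/60 = 7.3 points.

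**Equal proportional loss.** Dropping 10% of each arm gives 21/27 = 42/54 = 77.8%, a difference of 0. The distortion of the comparison needs unequal losses.

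**Dependence on the leavers' outcome.** Keep the control rate at 21/30, but let j of the 3 dropped controls have been cured. The retained rate is (21 − j)/27: 77.8%, 74.1%, 70.4% and 66.7% for j = 0, 1, 2 and 3. The 7.8 points are therefore the case in which no leaver is cured.

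**Power.** For assumed rates of 50% v 75% at two-sided 0.05, power is 65.7% with 30 v 60 and 63.0% with 27 v 60. The issue is bias much more than power.

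**The case against.** The strongest reply is that few patients, or none, may fall into the gap. No delay between randomisation and first dose is stated. The two-week allowance in section 3.3.2 runs from the end of selection, and footnote c puts the pregnancy waiting period before randomisation. A reader might infer a two-week window in which allocated patients can change their minds; the text does not support that. This part of the objection stands and limits the likely size.

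Second, a reader might infer that withdrawn patients are analysed only if tested. Section 3.2.3 does not say so. It speaks of possible inclusion, and only for patients who ask to withdraw. Footnote b plans a full evaluation for everyone who withdraws, and the visit at which treatment ends includes lesion size, parasitology and photographs. Nor does the section say that patients withdrawn for intolerance or lack of effect are left out. This also stands. What remains is that the wording ties inclusion to tests, and that an evaluation when treatment stops does not supply the 6-month endpoint.

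Third, analysis populations and missing-outcome rules are commonly left to an SAP, which is not at hand. That is right, and their absence is no part of this point. The point is a rule that the protocol does state. An SAP that analysed all randomised patients would have to override section 3.2.3, and it could not recover 6-month outcomes that sites did not collect because a patient was logged as a selection failure.

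Fourth, unequal loss is not documented. One might expect more refusals in the injection arm, since the Background calls antimony difficult to give in poor rural areas, but the protocol has no figure for this. Unequal loss is a risk, not a fact.

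**Conclusion.** The point holds in limited form. Section 3.2.3 puts the cut-point at first exposure when it should be at randomisation. It also links inclusion in the analysis of patients who request withdrawal to tests made after randomisation. In an open-label comparison of capsules with injections, this can remove randomised patients unequally by arm.

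The documents do not show that it will. The size depends on the unstated interval from randomisation to first dose, on how unequal the losses are, and on the leavers' outcomes. The 7.8-point figure is an illustration under the stated assumptions, not a forecast. Losses from the smaller control arm weigh about twice as much per patient as losses from the miltefosine arm.

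**What to change.** Change section 3.2.3 in three places:

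1. Restrict selection failure to exits before randomisation.
2. State that every randomised patient stays in the assigned arm in the primary cure-rate denominator, whether or not dosed and whether or not tested at withdrawal.
3. State that patients who stop study treatment but do not withdraw consent continue the visits already planned up to 6 months.

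The cost is protocol wording, since the visits are already in the flowchart. There is one small downside. If patients without a 6-month outcome count as not cured, the stated cure rates become slightly lower. That choice is not neutral: counting never-injected controls as not cured lowers the control rate and favours miltefosine, whereas dropping them raises it. A treated-and-assessed analysis should therefore be shown alongside, so that readers can see how far the result depends on the choice.

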#### Modifications in the treatment

Reduce dose: A patient who does not tolerate the dose of Miltefosine used, will leave the treatment. No dose reduction is planned.

Discontinuation of study treatment: The criteria for withdrawal are presented in section 4.2.3.

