#### Emergency measures

Adverse reactions known and associated with more intense dosing regimen proposed for Miltefosine are vomiting and diarrhea.

There must be an attentive observation and given the appropriate supportive treatment, adverse drug reactions suggested should be treated symptomatically.

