#### *Variable security:*

Vital parameters

Adverse Events

Laboratory tests (CBC, clinical biochemistry, urine)

Pregnancy test in women who may become pregnant

*Overall assessment:* Reason for discontinuation, overall assessment of tolerability  
A variation of the assessments plus / minus 2 days is acceptable. If these variations are not met, the reason should be documented in the appropriate page of medical records.

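### Section 3.2.3 has no tolerance category for a drug-related stop below grade 3 or made before confirmation, although the protocol provides for such stops

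*Protocol*

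**What the plan says.** Section 3.2.3 lists the withdrawal reasons. *Lack of tolerance* is "the dose-limiting intolerance reported by patients or observed by the doctor and found to be" probably related to study treatment. The next sentence makes an adverse event dose-limiting if it is "grade 3 or 4 of the common terminology criteria for adverse events (CTCAE) and is confirmed by a re-assessment within a week".

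Two further sentences in 3.2.3 deal with liver findings. For a grade 3 transaminase rise, "the investigator may decide to continue treatment until no manifestation of liver injury is observed" (apparently meaning for as long as none is seen), with extra control tests. Grade 4 enzyme elevation or clinical signs of liver damage "require immediate discontinuation of study treatment".

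Under 3.3.3, the paragraph on modifications in the treatment says: "A patient who does not tolerate the dose of Miltefosine used, will leave the treatment. No dose reduction is planned". It gives no grade and no confirmation step. For the withdrawal criteria it points to section 4.2.3, but they stand in 3.2.3.

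The other reasons in 3.2.3 are lack of effectiveness, intercurrent disease (causality unlikely or not assessable), withdrawal of consent or non-adherence, and a residual category. Section 4.3 has the end-of-treatment assessments done whenever treatment is discontinued, among them "Reason for discontinuation, overall assessment of tolerability".

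**The concern.** The reason code for a toxicity stop depends on a severity threshold and a later re-assessment, while other rules end treatment without either. A patient can therefore leave because of a probably related reaction and still not meet the only definition under which that stop counts as intolerance.

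Safety against antimony is part of the objective in section 2. A reader of the results will look at how many patients in each arm stopped because they could not tolerate the drug, and the coded reason is the natural source for that count. Under Emergency measures the protocol says the known reactions to the "more intense dosing regimen proposed for Miltefosine are vomiting and diarrhea". When rated probable, these two are kept off the adverse event form and go to separate modules, for which only intensity is specified (section 3.4). For them, the reason for discontinuation is the only stated record that the reaction ended treatment.

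**Working it through.** The protocol gives no intolerance rate, stop rate or resolution rate, so there is no figure to reproduce. The check sets the rules side by side.

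**Step 1: conditions for *Lack of tolerance*, read literally (3.2.3).** All three must hold: (i) probably related; (ii) CTCAE grade 3 or 4; (iii) confirmed by re-assessment within a week.

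**Step 2: stops that the protocol provides for without (ii) or (iii).** Grade 4 enzymes or clinical liver damage: immediate stop, so any re-assessment falls after it. Intolerance of miltefosine: the patient leaves, at no stated grade.

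**Step 3: apply the conditions to example cases, all rated probable.**

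| Case | (ii) grade 3-4 | (iii) confirmed | Code, read literally |
|---|---|---|---|
| Grade 3 transaminases, treated through, still grade 3 at re-assessment, then stopped | yes | yes | Lack of tolerance |
| Grade 4 enzymes, stopped at once, below grade 3 when re-assessed within the week | yes | no, if confirmed means still present | not Lack of tolerance |
| Grade 3 vomiting, patient leaves treatment, resolved before re-assessment | yes | no, on the same reading | not Lack of tolerance |
| Persistent grade 2 vomiting, patient leaves as not tolerating the dose | no | not reached | not Lack of tolerance |

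The last case needs no assumption about timing or about what confirmation means.

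**Step 4: where the last three cases go.** *Intercurrent disease* is closed to them, because it requires causality to be unlikely or not assessable. *Lack of effectiveness* does not describe them. *Other* or *Withdrawal of consent / non-adherence* remains.

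**Step 5: timing of the record.** Section 4.3 has the reason for discontinuation recorded when treatment stops. After an immediate stop the confirming re-assessment has not yet happened. In the section 4.6 flowchart the next visit after end of therapy is at 2 weeks, and CBC and biochemistry next appear at 1 month. If the on-treatment visits (days 7, 14, 21) end with treatment, no scheduled laboratory test falls within the week, and confirmation depends on an unscheduled one.

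**Step 6: size per patient.** Section 3.2 plans 60 patients on miltefosine and 30 on control. One stop coded elsewhere lowers the *Lack of tolerance* proportion by 1/60 = 0.0167, or 1.7 percentage points, on miltefosine, and by 1/30 = 0.0333, or 3.3 points, on control.

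**The case against.** The strongest reply has four parts.

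- **Terms.** *Lack of tolerance* is defined by dose-limiting intolerance, while the grade 3-4 sentence defines dose-limiting toxicity. An investigator could treat these as different and code any patient who does not tolerate the dose as *Lack of tolerance*. This is a fair reading. But the protocol gives no other meaning for dose-limiting, so two investigators could code the same stop differently. Similarly, the text does not say whether confirmed means still grade 3-4 or merely verified. The middle two cases in the table depend on that, but the grade 2 case does not.
- **Timing.** A reader might infer that treatment has always stopped before the re-assessment. The documents do not support this. Section 3.2.3 has no general rule to that effect and lets treatment continue through a grade 3 transaminase rise. Only the grade 4 enzyme and clinical liver damage rule forces the order.
- **Safeguards.** Section 3.2.3 requires *Other* reasons to be specified, and requires a check on whether an adverse event lay behind a consent withdrawal. A misfiled stop can thus be traced patient by patient. This stands and limits the harm, but it does not correct the coded tally.
- **Endpoint.** Section 2 names incidence and severity of adverse events, not a count of tolerance withdrawals. Section 3.4 documents all events on treatment without a confirmation step, and has an abnormal routine safety finding that led to premature discontinuation entered on the adverse event form. This stands, and the endpoint is intact. But the items listed for the adverse event record are dates, severity, seriousness and causality, not whether the event ended treatment.

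**Conclusion.** The point holds as a classification gap, and it is minor. Sections 3.2.3 and 3.3.3 are not aligned: the protocol provides for toxicity stops that its own *Lack of tolerance* definition, read literally, excludes. Each such stop takes 1.7 points (miltefosine) or 3.3 points (control) off the coded intolerance rate. This rests on reading dose-limiting intolerance and dose-limiting toxicity as the same thing. For the grade 3-4 cases it also rests on reading confirmation as persistence.

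Two stronger conclusions might be inferred, and the documents support neither.

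- **A stated share of toxicity stops is lost.** Any such percentage is one minus an assumed share of events still grade 3-4 at re-assessment, and the protocol gives no basis for that share. Section 5.2 calls the main adverse effects of miltefosine rarely dose-limiting, so few patients may be affected.
- **The rule favours miltefosine.** The definition in 3.2.3 is not specific to an arm, and nothing in the protocol says that vomiting or diarrhoea clears faster off drug than antimony toxicity does. One misfiled control patient also moves that arm's rate twice as far. A difference between arms is possible, but its direction and size cannot be derived.

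**What to change.** Reconcile 3.2.3 with the paragraph on modifications in the treatment as regards classification:

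- Code as *Lack of tolerance* every permanent stop for an adverse event rated probably related, whatever its grade and whether or not a re-assessment confirms it.
- Record confirmed grade 3-4 dose-limiting toxicity as a separate label.
- Report both by arm.
- Correct the cross-reference from 4.2.3 to 3.2.3.

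The clinical rules on stopping and continuing treatment stay as they are, and no view is taken on them here. The cost is a sentence in 3.2.3 and a matching change to the discontinuation coding, with no new visit, test or staff. The one drawback is that the reported intolerance rate may look somewhat less favourable.

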A The term "life threatening" in the definition of "serious" refers to an event in which the patient is at risk of death at the time of the event, does not refer to an event that hypothetically might have caused the death would be more serious.

B clinically important conditions that may not result in death, be life-threatening or require hospitalization may be considered when SAE, based on appropriate clinical trial, may involve risk to the patient or require intervention to prevent one of the outcomes listed in the above definition .

Note: The term "severe" is often used to describe the intensity (severity) of an event (as in mild pain, moderate or severe), the event itself may be of relatively minor clinical significance (such as severe headache). Not the same as "serious", which is based on the outcome of event / patient or action criteria usually associated with events that pose a risk to the patient's life or vital function. Seriousness (not severity) serves as a guide for defining regulatory reporting obligations.

*Procedures in case of adverse events*

The investigator should ask the patient at each visit if he / she had any medical problem or not unusual.

All adverse events that occur during the study treatment should be documented, regardless of the assumption of a causal relationship in respective page of the report form (CRF). All symptoms / complaints that have occurred in the last 14 days before the first exposure to study treatment should be documented in "Complaints at Baseline" medical records.

The documentation of adverse events including start and end date, severity, according to the CTCAE criteria, and seriousness. The investigator should also assess the likelihood of a causal relation of adverse event to study medication as probable, not assessable, or unlikely. The information provided in the investigator's brochure can give support to this evaluation.

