### **5.2 Consideration of risk-benefit**

Cutaneous leishmaniasis is a disease that is associated with clinically relevant morbidity, especially if the infection is widespread, diffuse or involve children (20% of cases), evolve with secondary infection or present a difficult approach.

The current standard treatment is done with pentavalent antimonials. These drugs are parenteral use of exclusive and their use is associated with sometimes severe toxicity, including pancreatitis and cardiac arrhythmias. The restrictions also apply to the use of amphotericin B, a drug of second choice in the treatment of disease that is associated with the occurrence of medication-induced fever and renal dysfunction. Amphotericin B requires hospitalization with elevation in the final cost of treatment.

The miltefosine was safe and effective in treating patients with LC (and LV). Its main adverse effects are related to the gastrointestinal tract, the liver and renal function and rarely dose-limiting. The medication has the added advantage of oral administration.

Preclinical studies indicated a teratogenic potential of Miltefosine, but no clinical experience is available on the use of this medicine during pregnancy in humans. Therefore, pregnancy should be strictly avoided during this study and in a period of 2 months after treatment ends. Preclinical studies in rats showed a dose effect and time-dependent in male fertility, no corresponding toxicity was observed in dogs. The after-treatment of Indian patients males during the reproductive performance and semen analysis before and after the use of Miltefosine (Colombia) as well as after treatment only (in India) did not suggest an adverse effect of Miltefosine on the male fertility.

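### Treatment stops whose causality cannot be judged are filed as intercurrent disease with no evidence of a drug relation, so stops for intolerance can be undercounted

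*Protocol*

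**What the plan says.** Protocol section 3.2.3 (Criteria for withdrawal) sorts premature stops by reason. Two of the reasons depend on causality.

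- **Lack of tolerance** covers dose-limiting intolerance "found to be 'probably' related to study treatment (and therefore does not refer to an aggravation of a preexisting condition").
- **Intercurrent disease** covers "A disease or condition that occurred or worsened during the study and prevented the completion of treatment and procedures of the study", with "no evidence of a causal relationship to study treatment, the adverse event record corresponding to classify causality as 'unlikely' or 'not assessable".

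The grades come from section 3.4, under the procedures for adverse events: "The investigator should also assess the likelihood of a causal relation of adverse event to study medication as probable, not assessable, or unlikely". There is no 'possible' grade, and none of the three is defined.

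The paragraph on modifications of treatment (section 3.3.3) explains why the reason for stopping carries information: "A patient who does not tolerate the dose of Miltefosine used, will leave the treatment. No dose reduction is planned". Section 4.3 has the reason for discontinuation recorded at the end of treatment.

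**The concern.** The intercurrent-disease definition joins two different statements. 'Unlikely' is a judgement against a drug relation. 'Not assessable' is the absence of a judgement. Calling both a lack of evidence for a relation turns missing information into a negative finding.

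The same section defines dose-limiting toxicity by a confirmed CTCAE grade 3 or 4 alone, without reference to causality. A patient could therefore have an event that the protocol calls dose-limiting, stop because of it, be rated 'not assessable', and appear in the results as an intercurrent illness unrelated to treatment.

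The parenthesis about aggravation raises a second problem. It treats a probable drug relation and a worsened preexisting condition as mutually exclusive, although a drug can worsen an abnormality that was already present.

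What is at stake is how tolerability is read from the withdrawal reasons. Safety is part of the objective (section 2). With no dose reduction planned, stopping is a direct marker of miltefosine intolerance. The trial is open label, so causality is rated with the arm known.

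**Working it through.** The protocol states no figure on this point, so there is none to reproduce. The check sets the definitions side by side and then scales the effect of one stop.

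**Step 1. Cross the causality grades (section 3.4) with the withdrawal reasons (section 3.2.3), read literally.**

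| Condition that ended treatment | Probable | Not assessable | Unlikely |
|---|---|---|---|
| New during the study | Lack of tolerance, if dose-limiting | Intercurrent disease | Intercurrent disease |
| Worsening of a preexisting condition | Neither of the two | Intercurrent disease | Intercurrent disease |

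- The 'not assessable' column gets the same label as 'unlikely' in both rows. No 'not assessable' stop can reach lack of tolerance.
- The lower left cell is a gap. Lack of tolerance excludes aggravation, and intercurrent disease requires one of the other two grades. By elimination such a stop would fall to the residual 'other reasons' category, which is also outside the intolerance count.

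**Step 2. Direction.** Both features can only take stops out of the intolerance count; neither can add one. Within an arm, the effect of the rule is zero or downward.

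**Step 3. Size per stop.** The inputs are the planned arm sizes in section 3.2: 60 on miltefosine and 30 on antimony.

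- Miltefosine: 1/60 = 1.7 percentage points.
- Antimony: 1/30 = 3.3 percentage points.

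**Step 4. Range.** The protocol gives no expected number of such stops. If 1 to 3 miltefosine stops are affected (an assumption), the undercount is 1/60 = 1.7 to 3/60 = 5.0 points.

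**Step 5. Effect on the comparison.** The rule refers to study treatment and so covers both arms. One misfiled stop in each arm lowers miltefosine by 1/60 and antimony by 1/30, which shifts the difference by 1/30 − 1/60 = 1/60 = 1.7 points, to miltefosine's disadvantage. The direction of any distortion between arms therefore depends on how many stops are misfiled in each arm, which is unknown.

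**The case against.** The strongest reply is that no endpoint depends on these categories. The safety endpoint in section 2 has no causality filter, and section 3.4 requires all adverse events on treatment to be documented whatever their presumed cause. This stands: the endpoint is not affected, and the point is confined to the reason-for-withdrawal table.

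A related reply is that the information is kept. An intercurrent-disease stop has an adverse event record with its own grade, and a routine safety finding that led to discontinuation must go on the adverse event form. This stands in large part. However, the fields that section 3.4 lists for an adverse event are dates, severity, seriousness and causality. Whether the event ended treatment rests mainly on the recorded reason for discontinuation, which is the item this rule mislabels.

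Three stronger readings are tempting, and the document does not support them.

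- *A reader might infer that an investigator who suspects the drug is forced to choose 'not assessable' or 'unlikely'.* The grades are undefined, and such an investigator may choose 'probable'. The missing 'possible' grade could push doubtful cases either way.
- *A reader might infer that drug-related worsening of an existing condition is filed as intercurrent disease.* If it is rated 'probable', it does not meet that definition. The parenthesis can also be read as a consequence of relatedness (a drug effect, not progression of the old illness). The wording is unclear and leaves a gap. It also does not say that a mildly raised laboratory value at entry is a preexisting condition.
- *A reader might infer that the rule builds in a favourable tolerability result.* The statement in section 5.2, "Its main adverse effects are related to the gastrointestinal tract, the liver and renal function and rarely dose-limiting", is risk-benefit background and not a result this trial is set up to claim. The rule applies to both arms.

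**Conclusion.** The point holds in a limited form. Section 3.2.3 wrongly equates 'not assessable' with no evidence of a drug relation, and it leaves a probably related worsening in neither of the two causality-based categories. Intolerance stops can therefore be undercounted in the reason-for-withdrawal table, by 1.7 points per stop with miltefosine and 3.3 points with antimony at the planned arm sizes.

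One cannot say that intolerance will be undercounted, or by how much: the protocol gives no number of such stops, and any total, including the 1.7 to 5.0 points above, rests on an assumed count. Nor is a bias between arms shown; open-label rating makes an arm-dependent effect possible, not established. The correction is still worth making, because it is cheap and the reason is classified when it is recorded. A later analysis could add a table that ignores causality, but it would leave the definition as it is.

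**What to change.** In section 3.2.3 and on the end-of-treatment form:

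1. Limit the category described as having no evidence of a causal relationship to stops rated 'unlikely'.
2. Record adverse-event stops rated 'not assessable' as a separate reason. Moving them all into lack of tolerance would only reverse the error, because illnesses nobody could attribute would then count as drug intolerance.
3. Reconcile the aggravation parenthesis with the intercurrent-disease definition, so that a probably related worsening has a category.
4. Base the between-arm tolerability comparison on all stops due to any adverse event, regardless of causality, with a breakdown by causality grade. The count should also draw on the separate vomiting and diarrhoea modules in section 3.4, because those reactions are kept off the adverse event form when rated 'probable'.

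The paragraph on modifications of treatment refers to the withdrawal criteria for discontinuing treatment. The edit should therefore state that it concerns only how a stop is classified and reported, and leave every clinical stopping rule as it is.

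The cost is a few lines of wording and one form field. The small downside is that the reported rate of adverse-event stops may look slightly less favourable.
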